## Abstract

**Background:**

Bisphosphonates are common first line medications used for the management of benign bone disease. One of the most devastating complications associated with bisphosphonate use is osteonecrosis of the jaws which may be related to duration of exposure and hence cumulative dose, dental interventions, medical co-morbidities or in some circumstances with no identifiable aggravating factor. While jaw osteonecrosis is a devastating outcome which is currently difficult to manage, various forms of delayed dental healing may be a less dramatic and, therefore, poorly-recognised complications of bisphosphonate use for the treatment of osteoporosis. It is hypothesised that long-term (more than 1 year's duration) bisphosphonate use for the treatment of post-menopausal osteoporosis or other benign bone disease is associated with impaired dental healing.

**Methods/Design:**

A case-control study has been chosen to test the hypothesis as the outcome event rate is likely to be very low. A total of 54 cases will be recruited into the study following review of all dental files from oral and maxillofacial surgeons and special needs dentists in Victoria where potential cases of delayed dental healing will be identified. Potential cases will be presented to an independent case adjudication panel to determine if they are definitive delayed dental healing cases. Two hundred and fifteen controls (1:4 cases:controls), matched for age and visit window period, will be selected from those who have attended local community based referring dental practices. The primary outcome will be the incidence of delayed dental healing that occurs either spontaneously or following dental treatment such as extractions, implant placement, or denture use.

**Discussion:**

This study is the largest case-controlled study assessing the link between bisphosphonate use and delayed dental healing in Australia. It will provide invaluable data on the potential link between bisphosphonate use and osteonecrosis of the jaws.

## Background

Bisphosphonates are non-metabolised analogues of pyrophosphates that are often prescribed to treat osteoporosis, Paget's disease of bone, metastatic osteolytic lesions associated with breast cancer, multiple myeloma, severe forms of osteogenesis imperfecta and moderate to severe hypercalcemia associated with malignancies [1-4]. In recent times intravenous bisphosphonates have also been advocated for the management of osteoporosis [5-7].

Post-menopausal osteoporosis is a common condition [8]. Less potent bisphosphonates such as alendronate and risedronate are first-line therapy for the treatment of post-menopausal osteoporosis, especially following a minimal-trauma fracture [9-11]. Paget's disease is another relatively common benign bone disorder for which bisphosphonates are first-line treatment [12]. By 2006, over 19 million prescriptions for bisphosphonates were dispensed worldwide suggestive of a good safety profile and benefit in osteoporosis management [13].

Adverse events related to bisphosphonate usage have centred largely around gastrointestinal and renal safety, bone, joint or muscle pain and the development of acute phase reactions [14]. Several recent reports have highlighted the possible association between bisphosphonate use, especially intravenous (IV) zoledronate or pamidronate, and jaw osteonecrosis [15-21]. Other studies have not found any association between bishosphonate use and ONJ [6]. A study assessing once yearly zoledronate for osteoporosis management in 8000 individuals reported, following separate case adjudication, a single episode of ONJ in each of the placebo and zoledronic acid groups [6]. The length of this study was only three years whereas most ONJ has been reported in patients taking bisphosphonates for longer periods of time. In a recent survey of over 8000 respondents, ONJ had a prevalence of 0.10% (95% confidence interval 0.05% to 2.0%)[22]. Previously, similar but less frequent presentations with jaw osteonecrosis occurred following radiotherapy (Ruggerio et al., 2004) or occupational exposure to phosphorus [23]. In many of the reports, jaw osteonecrosis occurred in the setting of malignancy, in particular, multiple myeloma [24-26] or breast cancer [18,19,26]. Recent work has suggested that in myeloma patients, zoledronate and pamidronate are associated with a 10% and 3% incidence of jaw osteonecrosis at 36 months, respectively [25]. In contrast, the prevalence of jaw osteonecrosis with bisphosphonate treatment in a large retrospective case series was 2.4% among myeloma patients and 1.2% among breast cancer patients [26].

There is some published evidence that chronic low-dose bisphosphonate treatment for osteoporosis or other benign bone disease is associated with jaw osteonecrosis [18,27]. However, randomised controlled trials of bisphosphonates in osteoporosis have not demonstrated an increased risk of jaw osteonecrosis. The development of ONJ has been linked to duration of exposure to bisphosphonates, and hence a higher cumulative dose, longer duration of treatment, hence prolonged survival, as well as potential co-morbidities such as prednisolone or thalidomide use [26]. Poor periodontal status together with dental interventions, in particular extractions, implants or trauma from dentures for example, significantly increase the risk of developing ONJ in this patient cohort [17,19,20,26,28].

The exact mechanism by which bisphosphonates may contribute to impaired resistance to injury or impaired healing of the maxilla or mandible and to osteolytic destruction, remains unclear. However, suppression of bone turnover via actions on osteoclasts seems to play a substantial role [29,30]. Bisphosphonates are not the only medications with this action. Other drugs such as denosumab (a RANKL antibody which is indicated in cancer patients) and bevacizumab (a human monoclonal antibody to vascular endothelial growth factor) have the potential to alter osteoclast differentiation and function and as such has also been implicated in ONJ [31,32].

Although ONJ associated with bisphosphonate use appears to resemble osteoradionecrosis seen following jaw radiotherapy, they are now considered different disease entities [33]. Conventional therapy of this latter complication involves local debridement, irrigation and antibiotics [34]. However, this strategy has yielded mixed results in bisphosphonate-associated osteonecrosis, and may contribute to further tissue breakdown, resulting in large fistulas [35].

While jaw osteonecrosis is a devastating end-stage outcome that is currently difficult to manage, various forms of delayed dental healing may be a less clinically dramatic and, therefore, poorly-recognised complications of bisphosphonate use. Currently, the likelihood of dental complications during bisphosphonate therapy for treatment of post-menopausal osteoporosis or other benign bone disease is uncertain. It is unclear what factors predispose patients to these events [36,37]. Given the large numbers of patients receiving long-term bisphosphonate therapy, particularly in benign bone disease, that a high level of professional and public concern has arisen about the issue, and the fact that we are living in an ageing population making the likelihood of levels of osteoporosis increasing, understanding the prevalence and risk of bisphosphonates and jaw osteonecrosis is paramount.

## Hypothesis

The hypothesis to be tested is that long-term (more than 1 year's duration) bisphosphonate use for the treatment of post-menopausal osteoporosis or other benign bone disease is associated with impaired dental healing.

## Methods

### Study design

A case-control study has been chosen to test the hypothesis as the outcome event rate is likely to be very low (Figure 1).

**Figure 1 F1:**
[figure not shown]
**Case-controlled study design**.

### Definitions

#### Delayed dental healing

Delayed dental healing (a precursor to osteonecrosis of the jaw) is defined as a persistent breach in the oral mucosa and/or exposure of bone in the mandible or maxilla that:

• fails to heal within 6 weeks as documented by a dentist despite usual therapy;

• occurs either following a dental procedure, for example a tooth extraction or crown insertion, or spontaneously, with or without osteonecrosis.

#### Osteonecrosis of the jaw

• Exposed bone in the maxillofacial area that occurred in association with dental surgery or spontaneously with no evidence of healing

• No evidence of healing after 6 weeks of appropriate evaluation and dental care

• No evidence of the following bone pathology that might explain the findings: metastatic disease in the jaw or osteoradionecrosis.

### Setting and study time frames

The study will take place in Victoria, the second most populous State in Australia with a population of approximately 5 million people. The visit window period study period will be March 1^st ^2006 until August 31^st ^2006. Participants in the study will have been treated in specialist oral and maxillofacial and special needs dentistry settings during the visit window period. Control subjects will have attended local community based referring dental practices. A flow diagram of the study protocol is depicted in Figure 2.

**Figure 2 F2:**
[figure not shown]
**Flow diagram of study protocol**.

### Dental Specialist Recruitment

Specialist dental recruitment will involve contacting all registered oral and maxillofacial surgeons and special needs dentists who were actively practicing during March 2006 through to the end of August 2006. All registered specialists listed in the Yellow Pages telephone directory will be cross-matched with those currently registered with the Australian Health Practitioner Regulation Agency. The researchers will also present the study to a Victorian Branch meeting of the Australian and New Zealand Association of Oral and Maxillofacial Surgeons. All public hospital dental specialty clinics in Victoria and associated specialist dental practitioners will be identified. All registered specialist dental practitioners will be invited to participate in the case-controlled study via introductory mail out.

Follow up of specialist non-respondents would occur by mail at 2-weeks and telephone at 4-weeks. Once specialists agree to participate, then the respective practice will be contacted to determine a suitable time to view patient files and identify potential cases. All files within the 6-month visit window period will be screened and only those meeting the age and visit window criteria will be reviewed for further potential case information. Once potential cases are determined then they will be presented to the Case Adjudication Panel (CAP) (see further details below).

### Case Recruitment

Recruitment of individuals for the study is a two-step process, ascertainment of potential cases through dental record review then verification by a case adjudication panel (CAP). The research team would visit each participating practice to identify potential cases from the dental records, which could then in turn be presented to the case adjudication panel. Each specialist practitioner would be required to give consent to have patients in their practice contacted by the research team.

Participant ascertainment will occur through consecutive screening of oral and maxillofacial and special needs dental specialist records in private practices and public hospitals by trained research staff. Once a case has been confirmed by CAP, each specialist practitioner would be required to give consent to have patients in their practice contacted by the research team.

To be eligible for participation, the dental record should indicate that the potential participant is:

• age ≥ 50 years

• has a dental wound that failed to heal within 6 weeks

• had a qualifying visit during the window period.

The exclusion criteria are:

• A history of active malignancy or malignancy within five years (excluding basal or squamous cell carcinoma).

• Previous radiotherapy field that included the jaws.

• Bisphosphonate use for any indication other than post-menopausal osteoporosis or other benign bone disease.

In order for potential cases to be identified from the patient files, the research team reviewing the clinical notes need to be able to identify delayed dental healing. It is expected that the term "delayed dental healing" as a potential descriptor is unlikely to appear in the clinical notes, as there would be variability in clinical descriptions amongst specialists. As such a number of file terminology descriptors will be used to help identify potential cases of DDH and these are outlined within 'data collection methods' below.

All records identified as potential cases of delayed dental healing will be presented to the CAP for verification for inclusion or exclusion. The CAP will include a Chair who will be an independent specialist endocrinologist, 2 other medical practitioners and three dentists (one Oral Medicine Specialist, one oral and maxillofacial surgeon and one forensic dentist/bone biologist). A quorum of 4 (2 dental and 2 medical) will be required at each CAP meeting.

At each CAP meeting all de-identified potential cases will be presented without the panel's knowledge of bisphosphonate history and medical status. The records presented will be assessed according to the previously stated inclusion and exclusion criteria.

Once verified as a definite case by the CAP, the individual will be contacted via mail to seek informed written consent for participation in the study. Non-responders will consist of two main groups; individuals who do not wish to participate and those who cannot be contacted (e.g. changed address or deceased).

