#### Part two: Delayed dental healing information

Each patient file identified within the visit window period will be analysed and information relating to the presence of an oral diagnosis (diagnosis, site, precipitant, treatment, outcome, biopsy report, radiographic investigation), bisphosphonate history and medical history (co-morbidities and medications) will be recorded.

The diagnosis will consist of the presence of either oral ulceration ("break in mucosa but no bone visible") or bone necrosis defined as "bone on view". A number of key words will be used when reviewing patient histories as a number of descriptors can be used to describe delayed dental healing. These will include non-healing socket, pus, exudate, swelling, draining sinus, dry socket, bone sloughing, sore sockets, OAC, oroantral communication, healing not completed, fistula, OAF, oroantral fistula, exposed bone and infection.

Information regarding site of the lesion will be further subdivided into single versus multiple sites, quadrant involved, palatal, lingual, buccal or labial orientation and tooth area (one to eight). The main precipitants listed can include tooth extraction, implant insertion, removal of pathological lesion, denture use, spontaneous, no obvious precipitant or other. In each case the date of the precipitant will be recorded. If the precipitant is not recorded in the history this will be marked as such on the data collection form.

Outcome of the delayed dental healing will be recorded by including treatment modalities such as antibiotics, mouthwashes/irrigation, debridement or other, date of the last review together with wound status (healed completely, healed partially, no healing or not recorded) and progress of the wound at the last visit (worse, stable, improving or not recorded). Details regarding any biopsy or radiographic analysis will also recorded.

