The prevalence of DDH in the target population will be estimated using data collected to determine case numbers in both bisphosphonate-treated and non-bisphosphonate-treated patients. We will also record cases of DDH occurring in non-bisphosphonate-treated patients with a diagnosis of benign bone disease where bisphosphonates may be indicated (i.e. osteoporosis, Paget's disease of the bone).

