### Outcome measures

#### Primary outcome measures

The primary outcome will be the incidence of delayed dental healing that occurs either spontaneously or following dental treatment such as extractions, implant placement, or denture use.

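### Case entry by visit date mixes new and long-standing wounds, so the odds ratio may reflect persistence as well as occurrence of delayed healing, and it should not be labelled incidence

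*Protocol article*

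**What the plan says.** Three sections of the protocol article fix who can be a case.

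- Setting and study time frames: "Participants in the study will have been treated in specialist oral and maxillofacial and special needs dentistry settings during the visit window period". The window runs from 1 March to 31 August 2006.
- Dental Specialist Recruitment: "All files within the 6-month visit window period will be screened and only those meeting the age and visit window criteria will be reviewed".
- Case Recruitment: the person is at least 50, "has a dental wound that failed to heal within 6 weeks" and "had a qualifying visit during the window period". The word *qualifying* is not defined.

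None of these ties the start of the wound, or its 6-week point, to the window. There is a lower limit on wound age (6 weeks) but no upper limit.

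Dates bearing on onset are collected. Part 1 of the data collection records when the oral problem presented and when it was referred. Part two states: "In each case the date of the precipitant will be recorded". No stated rule uses these dates to separate new from existing wounds.

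On the measure, Primary outcome measures says: "The primary outcome will be the incidence of delayed dental healing that occurs either spontaneously or following dental treatment". The Abstract says the same. The section Power and sample size plans a logistic model for the association with bisphosphonate use, and closes with: "The prevalence of DDH in the target population will be estimated using data collected to determine case numbers".

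**The concern.** Sampling on a visit captures whatever is under care during the window. A wound from 2005 still under review in March 2006 qualifies as readily as one that arose in April. A wound under care for a year has more chance of a visit in the window than one that closes in eight weeks.

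This matters because the outcome is itself about slow healing. If bisphosphonate users' wounds stay open or under review longer, users will be over-represented among cases even if they develop delayed healing no more often. A reader who sees incidence named as the primary outcome, and a Discussion that hopes to estimate the true risk with exposure, would take a raised OR to mean that more wounds become delayed. It could instead mean that delayed wounds last longer, or some of both. The limitations in the Discussion cover practitioner and patient participation, record quality and recall, but not this.

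**Working it through.** **1. The plan's own figure.** Inputs from Power and sample size: 10% exposure in controls, 30% in cases, 4 controls per case, 90% power. The OR is (0.30/0.70)/(0.10/0.90) = 3.857, against the stated 3.85. A two-proportion calculation with continuity correction and an assumed two-sided 5% level gives 54 cases + 216 controls = 270, against the stated 54 + 215 = 269. The sample size reproduces and is not in question.

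**2. What visit-based entry does.** Let W = 6 months be the window and D the mean time a delayed wound stays under specialist care. Assume a steady rate of new delayed wounds, and that a wound under care during the window has a visit in it. A wound is then sampled if it came under care at any time from D months before the window opened until the window closed. So:

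- chance of being sampled is proportional to occurrence × (W + D);
- share of sampled cases dating from before the window = D/(W + D);
- sampled OR = occurrence OR × (W + D_exposed)/(W + D_unexposed).

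The share dating from before the window is 3/9 = 33% at D = 3 months, 6/12 = 50% at 6 and 12/18 = 67% at 12.

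**3. OR when exposure has no effect on occurrence.** All durations are assumptions; the document gives none.

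| D unexposed (months) | D exposed (months) | OR |
|---|---|---|
| 3 | 3 | 9/9 = 1.00 |
| 3 | 6 | 12/9 = 1.33 |
| 3 | 9 | 15/9 = 1.67 |
| 3 | 12 | 18/9 = 2.00 |
| 12 | 36 | 42/18 = 2.33 |
| 6 | 3 | 9/12 = 0.75 |

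The first row shows that over-sampling long wounds does not distort the OR by itself: a difference in time under care by exposure is needed. The last row shows that the distortion can run the other way.

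**4. What this could do at the planned size.** With 54 cases, 215 controls and 10% exposure in controls, sampled ORs of 1.33, 1.67 and 2.0 give about a 10%, 24% and 40% chance of a significant result towards harm. The nominal chance is 2.5% in that direction (two-sided 5% assumed, normal approximation, matching ignored). These figures are without continuity correction; a corrected test gives lower ones. Read the other way, a sampled OR of 3.85 would correspond to an occurrence OR of 3.85 with equal durations, 3.85/1.33 = 2.89 in the second row and 3.85/2.33 = 1.65 in the fifth.

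**5. Whether the collected dates can separate the two.** A wound that reached 6 weeks (42 days) between 1 March and 31 August 2006 had its precipitant between 18 January and 20 July 2006. The precipitant date settles this where it exists. Part two also allows for wounds that arose spontaneously, had no evident trigger, or have no precipitant noted. For those, only the presentation date from Part 1 is available, and that may be later than onset.

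**The case against.** Several points on the other side have force.

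- *Qualifying* may be defined in the full protocol, and the flow diagram is not shown. This stands as a limit: the point concerns the entry rule as printed. But the screening and setting sections are also purely visit-based, and nothing printed gives the word an onset meaning.
- The Hypothesis is about impaired healing, and a longer-lasting wound is impaired healing. So an OR raised by duration is not plainly a false rejection of that hypothesis. This stands. The difficulty is confined to reading the OR as the risk of developing a delayed wound.
- A drug that slows healing would usually push more wounds past 6 weeks, so longer duration with no effect on occurrence is an extreme case. This stands too: the table isolates the sampling effect and does not forecast it.
- An analysis of new cases only might sit in an analysis plan that is not shown. Its absence is therefore not counted as an error. The point rests on the printed entry rule and the printed outcome label.

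A reader might infer that the visit rule biases the OR upwards. The document does not support that. Its Background says conventional management has given mixed results in bisphosphonate-associated necrosis. That makes longer care plausible, but it supplies no duration and no comparison by exposure for delayed healing in benign bone disease.

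A reader might also infer that limiting cases to new wounds would turn the OR into an incidence. It would not: a case-control OR is a relative measure however cases are sampled. The incidence label needs correcting in any event.

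**Conclusion.** The point holds in limited form. As printed, the entry rule mixes prevalent and incident wounds and favours those longer under care. The all-case OR therefore reflects occurrence and persistence together whenever time under care differs by bisphosphonate use.

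The size is unknown. Under a steady-state model with a 6-month window, the factor on the OR is 1.00 with equal durations and 1.33 to 2.0 with an assumed 3 months in unexposed and 6 to 12 months in exposed cases. It falls below 1 if exposed wounds are under care for less time.

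Separately, and whatever the durations, incidence is not what this design estimates, and it sits unreconciled beside the planned prevalence. The protocol itself says that relative or absolute risk would come from a cohort study. The all-case OR remains a useful result; what needs fixing is what it may be taken to mean.

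**What to change.** 1. Flag each case whose wound reached 6 weeks between 1 March and 31 August 2006, using the precipitant date, or the presentation date where there is no precipitant date. Report how many cases cannot be classified, by exposure.
2. Pre-specify the OR in the flagged cases as a sensitivity analysis beside the all-case OR. State that the all-case OR reflects occurrence and persistence together.
3. In Primary outcome measures and the Abstract, restate the primary measure as the odds ratio for bisphosphonate use in cases versus controls. Reconcile this with the prevalence estimate described under Power and sample size.
4. Define *qualifying visit*.

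Recruitment and the 54/215 target do not change. The work is one derived flag, one extra analysis and some rewording. The cost is precision: if mean time under care were 3 months, about 54 × 6/9 = 36 of the 54 cases would remain, and the interval would widen. Spontaneous or undated wounds may be unclassifiable, possibly unevenly by exposure. Using presentation dates will also class some older wounds as new.

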#### Part 3: Medical History

Detailed information relating to potential cancer history including type, date of diagnosis, remission status, radiotherapy to the jaw and chemotherapy will be recorded as this is a key exclusion criterion. Other co-morbidities will be recorded including lung disease, heart disease, kidney disease, organ transplant, diabetes, rheumatoid arthritis or other connective tissue conditions together with smoking, tobacco and alcohol intake as these may contribute to delayed dental healing.

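### The adjudication panel is masked to the very information that its exclusion criteria require, and the file review that selects its cases is not described as masked

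*Protocol article*

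**What the plan says.** The Case Recruitment section of the protocol article describes two steps: research staff find potential cases in specialist dental files, and a case adjudication panel then verifies them.

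On masking, it says that "all de-identified potential cases will be presented without the panel's knowledge of bisphosphonate history and medical status". On the panel's task, the following sentence says: "The records presented will be assessed according to the previously stated inclusion and exclusion criteria". The same section sends records to the panel to be verified for inclusion or exclusion.

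Three exclusions are listed there: malignancy that is active or within five years (with a skin-cancer exception), "Previous radiotherapy field that included the jaws", and "Bisphosphonate use for any indication other than post-menopausal osteoporosis or other benign bone disease".

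Part 3: Medical History collects cancer details and says that "radiotherapy to the jaw and chemotherapy will be recorded as this is a key exclusion criterion".

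Part two: Delayed dental healing information describes the file review. Along with the oral diagnosis, "bisphosphonate history and medical history (co-morbidities and medications) will be recorded". It also lists the key words used to recognise delayed healing, some of them broad (pus, swelling, infection).

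The Telephone interview section has every consenting participant interviewed, partly to confirm eligibility. This follows the panel's decision, because consent is sought only after a case has been verified.

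**The concern.** Panel masking is the main safeguard against bisphosphonate exposure influencing who is called a case. If the panel applies the exclusions, it must see the history it is supposed not to see. If it stays masked, it can judge age, the unhealed wound and the visit date, but none of the exclusions. The text does not say which of these will happen.

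The second issue lies upstream. Only files that staff identify as potential cases reach the panel. If knowledge of bisphosphonate use makes a reviewer more or less ready to flag an ambiguous file, exposure among cases is distorted before the masked step begins. In a case-control study that distortion passes straight into the odds ratio.

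**Working it through.** **1. Exclusions against masking.**

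| Exclusion (Case Recruitment) | Information needed | Masked from panel? |
|---|---|---|
| Malignancy, active or within five years | Cancer history, collected under Part 3: Medical History | Yes, medical status |
| Radiotherapy field including the jaws | Radiotherapy history, collected under Part 3 | Yes, medical status |
| Bisphosphonate for another indication | Drug and indication | Yes, bisphosphonate history |

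None of the three can be judged by a panel masked as described.

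**2. Where else the exclusions could be applied.** Between the panel's verification and the consent letter, no exclusion step is described. If file reviewers applied the exclusions before forwarding (not stated), they would have to read cancer and bisphosphonate history first. The interview comes after consent and covers consenting participants only. The last paragraph of Statistical Analysis plans a prevalence estimate from case numbers in treated and untreated patients, and does not say whether confirmed cases who do not consent are counted.

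**3. The plan's own figures, as a base.** Inputs from Power and sample size: 10% exposure in controls, 30% in cases, ratio 4:1, 90% power. Alpha is not stated there; two-sided 0.05 is assumed.

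- OR = (0.30/0.70)/(0.10/0.90) = 3.857, as stated (about 3.85).
- Pooled p = (0.30 + 4×0.10)/5 = 0.14. Uncorrected n' = [1.96√(5×0.14×0.86) + 1.2816√(4×0.30×0.70 + 0.10×0.90)]² / (4×0.20²) = 47.5, or 48 cases.
- With continuity correction: (n'/4)[1 + √(1 + 2×5/(n'×4×0.20))]² = 53.6, or 54 cases. Four controls each gives 216, against 215 stated. The plan's figure reproduces.

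**4. Illustration of exposure-dependent forwarding.** Assume no true effect, 10% exposure among true cases, and exposed cases forwarded r times as often as unexposed ones. Observed exposure among cases is p = 0.10r/(0.10r + 0.90), and the apparent OR is [p/(1−p)]/(0.10/0.90) = r.

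| r (assumed) | Exposure in cases | Apparent OR | Chance of a significant harmful finding, 54 vs 215 |
|---|---|---|---|
| 1.25 | 0.125/1.025 = 12.2% | 1.25 | about 8% |
| 1.5 | 0.150/1.050 = 14.3% | 1.5 | about 17% |

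The last column is Φ{[(p − 0.10) − 1.96·SE₀]/SE₁}, an unadjusted two-proportion test without continuity correction, where SE₀ is the pooled and SE₁ the unpooled standard error. For r = 1.5: (0.0429 − 1.96×0.0474)/0.0518 = −0.96, giving 0.167. The nominal chance in that direction is 0.05/2 = 2.5%. No value of r can be derived from the document, and r below 1 would bias the other way.

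**The case against.** A reader might infer that cancer or radiotherapy patients will end up among the analysed cases. The document does not support that. Part 3 records cancer and jaw radiotherapy expressly for exclusion, and the interview lets staff remove ineligible participants while the panel stays masked. One can calculate that if 5% or 10% of cases were malignancy patients with 80% exposure (all assumed), exposure among cases would be 0.95×0.10 + 0.05×0.80 = 13.5% or 0.90×0.10 + 0.10×0.80 = 17%. The OR under no effect would then be (0.135/0.865)×9 = 1.40 or (0.17/0.83)×9 = 1.84. Those figures apply only if the later check fails and controls contain no such patients. This part of the objection stands.

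A reader might also infer that the file reviewers are stated to be unblinded and that the odds ratio is inflated. Neither is stated. Reviewer masking and form order could sit in a fuller protocol. Consecutive screening by trained staff, a written key-word list and the rule that every identified record goes to the panel all limit discretion, and a broad list may favour inclusive forwarding. The Discussion already concedes researcher interpretation as a limitation. This part stands against any claim about the size or direction of bias. It does not remove the exposure: the described review takes diagnosis and bisphosphonate history from the same file, and flagging still needs judgement because, as the protocol notes, specialists' wording varies.

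The objection does not touch the conflict between the two adjacent sentences. The article states both, so this is not detail left to another document.

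**Conclusion.** The panel's instructions are wrong as written: it is told to apply exclusions that consist entirely of information withheld from it. This follows from the text alone and needs no assumption.

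Contamination of the analysed cases by ineligible patients is possible but not shown, because the interview gives a later route to exclusion. That route does not cover confirmed cases who do not consent, which matters only if they enter the prevalence estimate.

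That reviewers know exposure when they select files is a sound inference from the described file review, not a stated fact. If forwarding did depend on exposure, the panel could not correct it, and the odds ratio would be multiplied by the forwarding ratio. The range of 1.25 to 1.5 is an assumption that shows scale; the true size and direction are unknown.

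**What to change.** Three changes to Case Recruitment:

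1. State that the masked panel judges only whether the delayed-healing definition is met.
2. Have reviewers forward every record that meets a fixed rule (any listed descriptor documented as persisting beyond 6 weeks), regardless of bisphosphonate or medical history.
3. Apply the three exclusions by rule after the panel's decision, from the file record and the interview, identically to cases and controls, and report counts by reason. For confirmed cases who do not consent, say whether they enter the prevalence estimate and, if so, that the exclusions rest on the file alone.

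This needs no new data and no change in sample size. The cost is that some records are adjudicated and later excluded. The rule narrows discretion but does not remove it, since persistence must still be read from variable notes, and reviewers are not truly blinded because they read the whole file. Completing the bisphosphonate and medical sections only after the panel's decision would not change that, and could mean reopening files at each practice.
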